## **STUDY PROTOCOL**

### **Study design**

The study will adopt a cluster randomized bioequivalence trial with four study groups; zinc, zinc in multiple micronutrients and multiple micronutrients without zinc (experimental groups adding once daily Micronutrient Powders (sprinklestm) to corn-soy porridge) and a comparator group on daily conventionally fortified Corn-Soy Blend (CSB).

### **Study area**

The study will be based in Kiandutu and adjacent informal settlements, 40 km North of Nairobi, situated in Thika West District, Kiambu County, approximately 40 km north of the City of Nairobi. The district lies between latitudes 3°53' and 1° 45' South of Equator, longitudes 36° 35' and 37° 25' East and altitude 1631m above sea level. Kiandutu slum is a high density informal settlement with an estimated population of over 70,000 (2009 census report) and is one of the largest informal settlements located outside Nairobi, the capital city of Kenya. Kiandutu means a place of “jiggers” depicting poor living conditions (Koomen, 2012). The collapse of industries and coffee plantations in Thika District rendered most of the inhabitants jobless and hence the high poverty levels (Kinyanjui, 2007).

The study area will consist of twelve villages; Mtatu, Biashara, Muslim, Kianjau, Molo, Mkira, Wahome, Athena settlement, Makongeni, Umoja, Gachagi and Madharau. Two public health facilities are located in the study area; Kiandutu Health Centre (HC) and Makongeni Health Centre and are supported up-stream by Thika Level Five Hospital where referrals are made for the critically ill individuals. The study area was selected because research has shown that children living in informal settlements have a high prevalence of malnutrition aggravated by poverty, food insecurity, poor hygiene and sanitation and limited access to health services.

### **Baseline study**

At baseline, information on socio-economic status, vaccination status, appetite, morbidity patterns, dietary patterns, anthropometric measurements, serum zinc(zn), serum albumin and CRP of the children will be collected.

### **Intervention phase**

### **Target population**

The study will target Moderately Malnourished (MM) children 6-36 months old with height weight for height (WH) within -3 and less than -2 Z-scores or with/and a mid-upper arm circumference (MUAC) within the range of 115-125 mm without bilateral oedema. The age 6-36 months is a period of rapid growth, highest nutrient requirements and poor diets predispose children to a risk of zinc deficiency. The beneficial effect of zinc may be limited to children with pre-existing growth failure (IZiNCG, 2004b) hence the study targets MM children. The respondents will be the mothers/primary caregivers to the children.

### **Inclusion criteria**

MM children (6-36) months, whose parents consent, willing to be visited in their homes and intending to stay in the area during the study period and who will have stayed in the area for the past 6 months will be recruited.

### **Exclusion criteria**

The study will exclude severely malnutrition and bed-ridden children. Those with other conditions as verified from medical cards, review by a clinical officer, interview sessions and observations will also be excluded. Children taking micronutrient supplements (except Vit. A) and/or fortified foods for the past 3 months will also be excluded. This information will be verified from medical cards and recording of the supplements or fortified foods given to the child as indicated in the food labels.

### **Description of the intervention**

CSB (80% corn and 20% soy) and sprinkles meeting 100% RDA of zinc will be sourced from suppliers. For a period of six months, sprinkles (1g) will be added to corn-soy porridge once daily and CSB porridges made from 100g flour will be given daily (Figure 1). The micronutrient composition of the different study groups is shown in Table 1. The food supplements will be prepared in feeding centres. De-worming will be done at the start of the intervention using mebendazole (500 mg). Demonstrations on porridge preparation and use of sprinkle and nutrition education focused on the importance of nutritious diet will be given to the primary caregivers on group basis at baseline.

Table 1: Micronutrient composition of sprinkles and CSB

|                  | Expt Gp 1:
Sprinkles (per 1
g sachet) | Expt Gp 2:
Sprinkles* (per 1
g sachet) | Expt Gp 3:
Sprinkles* (per 1
g sachet) | Comparator Gp
4: CSB ( 100g
dry wt.) |
|------------------|------------------------------------------------------|-------------------------------------------------------|-------------------------------------------------------|-----------------------------------------------------|
| Vit A (IU)       | -                                                    | 1250                                                  | 1250                                                  | 1300                                                |
| Vit E (mg)       | -                                                    | 6.0                                                   | 6.0                                                   | -                                                   |
| Vit C (mg)       | -                                                    | 30                                                    | 30                                                    | 30                                                  |
| Thiamine (mg)    | -                                                    | 0.5                                                   | 0.5                                                   | 0.1                                                 |
| Riboflavin (mg)  | -                                                    | 0.5                                                   | 0.5                                                   | 0.4                                                 |
| Vit B6 (mcg)     | -                                                    | 0.5                                                   | 0.5                                                   | -                                                   |
| Niacin (mg)      | -                                                    | 6                                                     | 6                                                     | 5                                                   |
| Folic Acid (mcg) | -                                                    | 160                                                   | 160                                                   | 50                                                  |
| Vit. B12 (mcg)   | -                                                    | 0.9                                                   | 0.9                                                   | 1                                                   |
| Vitamin D3       | -                                                    | 5                                                     | 5                                                     | -                                                   |
| Calcium (mg)     | -                                                    | -                                                     | -                                                     | 100                                                 |
| Iron (mg)        | -                                                    | 12.5                                                  | 12.5                                                  | 8                                                   |
| Zinc (mg)        | 5                                                    | 5                                                     | -                                                     | 5                                                   |
| Iodine (mcg)     | -                                                    | 90                                                    | 90                                                    | -                                                   |
| Copper           | -                                                    | 0.3                                                   | 0.3                                                   | -                                                   |

### **Randomization**

The sampling frame will consist of the 12 villages in Kiandutu slum. Three villages will be randomly allocated to each of the 4 study groups. Villages rather than study subjects will be randomized to avoid cross-contamination of information due of the close proximity of the study subjects. Computer generated randomization will be done by a statistician.

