### 3.4.6 Sample size determination

Determination of sample size will be based on the primary objective and the formula by Liu

& Chow (1992). Where; 
$$n = \frac{(Z_{\alpha} + Z_{\beta})^2 \sigma^2}{(\delta - \varepsilon)^2} = \frac{(1.64 + 1.28)^2 0.71^2}{(0.2 - 1.0)^2} = 67$$

Where; n = No. of study subjects per group,  $\sigma$  = variance within the groups,  $\delta$  = expected outcome difference of the groups (20 % as per the bioequivalence rule),  $\varepsilon$  = the absolute values of proportion differences among the groups. The standard normal deviate at the required confidence interval (95 probability error).

The prevalence of zinc deficiency in Kenya is 50% (GOK & UNICEF, 2008). The estimated post-intervention prevalence of 20%, 10%, 20% and 50% for the reference, ZN, ZN in MMN and MMN without ZN groups respectively. To show equivalence within 20% rule with 80% power and 5% significance, a sample size of 67 per group was obtained and allowing 20% attrition, a sample size of 80 per group is obtained.

Where; n = The desired sample size, z = The standard normal deviate at the required confidence interval (95 probability error equal to 1.96), p = The proportion of occurrence of the phenomenon (0.5) since prevalence is 50%, q = The proportion of non-occurrence is (1-P) = 0.5, d = level of statistical significance (0.05 for 95% level of significance).

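### Twelve villages are randomised three per arm with no balance constraint, so chance imbalance between arms is likely and feeds into the equivalence comparison

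*Protocol*

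**What the plan says.** Study design describes a "cluster randomized bioequivalence trial with four study groups". The allocation rule is given in full under Randomization: "Three villages will be randomly allocated to each of the 4 study groups", and "Computer generated randomization will be done by a statistician". No stratification, blocking, matching or other balance criterion is mentioned.

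The protocol describes the location of the villages in two ways. Study area says "The study will be based in Kiandutu and adjacent informal settlements" and then "The study area will consist of twelve villages", which it names. Randomization says "The sampling frame will consist of the 12 villages in Kiandutu slum". Study area also notes that "Two public health facilities are located in the study area", but does not say which villages each one serves. Village sizes are not given.

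Data analyses bases the bioequivalence conclusion on whether the percentages of children with low serum zinc in the sprinkles and CSB groups agree within the ±20 rule, after excluding children with raised CRP. That rule states no adjustment. ANCOVA and regression are planned in the same section, but no village term is named.

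**The concern.** Each arm rests on three clusters. Enrolling more children per village does not average out differences between villages; only the allocation or an adjustment can limit them. If villages differ in underlying zinc deficiency, for example through access to care or living conditions, an uneven draw moves the difference in percentages directly. The shift can go either way: it can push an equivalent product outside the margin or make a non-equivalent one look acceptable.

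The allocation method belongs in the protocol, which has a section for it, so this is not a detail left to an analysis plan. It also cannot be repaired in the allocation once the villages have been assigned.

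**Working it through.** **Inputs from the protocol.** 12 villages (Study area, Randomization); 4 arms (Study design); 3 villages per arm (Randomization); a ±20 rule, read here as percentage points (Data analyses); 80 children per group including 20% attrition (Sample size determination). The stated allocation is consistent: 4 × 3 = 12.

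**Inputs that are assumed.** The villages fall into two types, and the rarer type has m villages. The protocol gives neither, so m is varied. The prevalence gap between types and the intracluster correlation (ICC) are also assumed.

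**1. Number of allocations.** 12!/(3!)^4 = 369,600.

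**2. Chance that at least one arm has no village of one type.** A pattern (a1, a2, a3, a4) of rarer-type villages across the arms has probability [C(3,a1) × C(3,a2) × C(3,a3) × C(3,a4)] / C(12,m). The patterns in which every arm has both types are:

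- m = 4: only (1,1,1,1), 3^4/C(12,4) = 81/495 = 16.4%. Some arm misses a type: 83.6%.
- m = 5: (2,1,1,1) in 4 orders, 4 × 81/792 = 40.9%. Some arm misses a type: 59.1%.
- m = 6: (2,2,1,1) in 6 orders, 6 × 81/924 = 52.6%. Some arm misses a type: 47.4%.
- m = 1 to 3: too few villages to go round four arms, so 100%.

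**3. Two given arms, such as one sprinkles arm and CSB.**

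| m | Differ by 2 or more of 3 villages | Fully separated (3 vs 0) | SD of the difference in share of the rarer type |
|---|---|---|---|
| 4 | 21.8% | 2.4% | 0.40 |
| 5 | 23.5% | 3.8% | 0.42 |
| 6 | 23.8% | 4.3% | 0.43 |

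The last column is √[8p(1−p)/11] with p = m/12. For m = 4, √(8 × 0.222/11) = 0.40. For m = 6, √(8 × 0.25/11) = 0.43.

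**4. Effect on the comparison.** A one-SD imbalance shifts the arm difference by the SD times the assumed prevalence gap between types:

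- gap of 10 points: about 4 points
- gap of 20 points: about 8 to 9 points
- gap of 30 points: about 12 to 13 points

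The margin is 20 points. The sample size section expects 20% deficiency in the reference group and 10% in the zinc group, which already uses 10 of them.

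**5. What blocking would do to precision.** Take 80 × 0.8 = 64 children per arm, or 64/3 = 21.3 per village. The variance of a village mean is proportional to ICC + (1 − ICC)/21.3. At ICC 0.05 this is 0.05 + 0.95/21.3 = 0.0945. If three blocks of four villages explain half the village variance, it falls to 0.0945 − 0.025 = 0.0695. Fitting the blocks cuts the degrees of freedom from 8 to 6, so the ratio of 90% interval half-widths is √(0.0695/0.0945) × 1.943/1.860 = 0.896. With 0%, 10% and 25% explained the ratio is 1.045, 1.017 and 0.973.

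The break-even share of village variance is the f that solves (V − f × ICC)/V = (1.860/1.943)², where V is the variance of a village mean. It is about 16% at ICC 0.05, 28% at ICC 0.02 and 47% at ICC 0.01.

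**The case against.** The strongest reply is that randomisation already deals with this. Chance imbalance is random error, and a valid village-level interval includes it. A reader might infer that villages and products become confounded. The protocol does not support that: allocation is random, each arm has three villages, and full separation of two given arms by type has a probability of about 4% or less. This part of the reply stands.

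The village types are also not in the protocol. A reader might take the 84% as a property of this trial, but it holds only if exactly four villages share a feature. A reader might likewise assume from Study area that the villages include neighbouring settlements, whereas Randomization places all 12 in Kiandutu. If Randomization is right, settlement drops out as a balancing factor, although villages in one slum may still differ in health-centre catchment and size. Study area does not show that catchments are distinct. These points stand, and they are why a range is shown.

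A third tempting inference is a 10% narrower interval at no cost in degrees of freedom. The two cannot be had together: the narrowing appears only if the analysis adjusts for the blocks. It also depends on the ICC and on the variance explained, and with weak blocks the interval widens.

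Finally, baseline data are collected and ANCOVA is planned. That could help, but the stated equivalence rule compares percentages without adjustment, so it is not clear that adjustment reaches the main decision.

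**Conclusion.** The point holds as a cheap, low-priority improvement. The protocol states no balance constraint for 12 villages in four arms, and the deciding comparison is exposed to village imbalance. For any two-type split, some arm misses a type in at least 47% of allocations, so imbalance of this kind is likely. How far it would move the result is unknown: the 8 to 9 points at one SD rest on an assumed 20-point gap between types.

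Fixed blocks of four are a debatable trade-off, given the break-even figures and the lack of any documented village grouping, and they are not pressed here. A constrained random draw does not need groups of four. If the rarer type has three or fewer villages, no allocation can place one in every arm; a constraint can then only stop them from clustering in one arm.

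The contradiction over where the villages lie is a separate textual fault. It must be resolved first, because it decides whether settlement is a balancing feature at all.

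**What to change.** 1. Reconcile Study area and Randomization on whether the 12 villages lie only in Kiandutu or also in adjacent settlements.
2. Before allocation, list simple features for each village: health-centre catchment, size, and settlement if it applies.
3. State in Randomization that the statistician will score the 369,600 allocations for balance on these features, fix in advance a sufficiently large set of the best-balanced ones, and draw one at random. For scale, even exact balance on three groups of four villages would leave (4!)^3 = 13,824 allocations, 3.7% of the total.
4. State whether the analysis will adjust for the balancing features. If it does not, a village-level interval stays valid but is conservative. If it does, any narrowing comes at some cost in degrees of freedom and depends on the ICC and the village variance explained, neither of which the protocol gives.

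The cost is compiling the feature list and a few lines of allocation code. No extra villages or children are needed.

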### **Data collection tools and procedures**

Baseline data on children's past and present illnesses will be obtained by interviewing the primary caregivers and from confirmation from health cards. A semi-structured questionnaire designed to elicit information on the household socio-economic, demographic structure, parental education and employment, material possessions and type of housing materials. A 24-hour recall designed for measuring nutrient intakes inclusive of zinc will be used and a Food Frequency Questionnaire (FFQ) will be administered to cover the most commonly consumed complementary foods based on a 7-day recall. Appetite will be assessed monthly using the Children's Eating Behaviour Questionnaire (CEBQ),

Serum zn, albumin and CRP will be determined at baseline and post-intervention. Monthly anthropometric measurements and dietary intake will be conducted monthly for the 6-month period. Interviewers will visit the childrens' homes bi-weekly to inquire about symptoms of illness (severity, frequency and duration) of diarrhoea, ARTI and other infections, and monitor the feeding practices.

### Training of research team

A research team comprising of a clinical officer, and 6 Research Assistants (RA's) (minimum education; K.C.S.E) and interviewers will be trained on the research aspects. The objectives will be explained without disclosing the research hypotheses. Interviewers will be trained on taking anthropometric measurements and interviewing skills taught through demonstrations and role plays. The investigator will test the RA's and interviewers for accuracy, consistency and logical recording skills, and corrective measures taken till the investigator was satisfied with the competence.

### 3.4.6 Sample size determination

Determination of sample size will be based on the primary objective and the formula by Liu

& Chow (1992). Where; 
$$n = \frac{(Z_{\alpha} + Z_{\beta})^2 \sigma^2}{(\delta - \varepsilon)^2} = \frac{(1.64 + 1.28)^2 0.71^2}{(0.2 - 1.0)^2} = 67$$

Where; n = No. of study subjects per group,  $\sigma$  = variance within the groups,  $\delta$  = expected outcome difference of the groups (20 % as per the bioequivalence rule),  $\varepsilon$  = the absolute values of proportion differences among the groups. The standard normal deviate at the required confidence interval (95 probability error).

The prevalence of zinc deficiency in Kenya is 50% (GOK & UNICEF, 2008). The estimated post-intervention prevalence of 20%, 10%, 20% and 50% for the reference, ZN, ZN in MMN and MMN without ZN groups respectively. To show equivalence within 20% rule with 80% power and 5% significance, a sample size of 67 per group was obtained and allowing 20% attrition, a sample size of 80 per group is obtained.

Where; n = The desired sample size, z = The standard normal deviate at the required confidence interval (95 probability error equal to 1.96), p = The proportion of occurrence of the phenomenon (0.5) since prevalence is 50%, q = The proportion of non-occurrence is (1-P) = 0.5, d = level of statistical significance (0.05 for 95% level of significance).

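### The printed sample-size equation evaluates to 6.7, not 67, and its group difference of 1.0 contradicts the protocol's own assumed prevalences, so 80% power at 67 per group is unsupported

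*Protocol*

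**What the plan says.** Section 3.4.6 (Sample size determination) prints the calculation, in typesetting code, as "1.64 + 1.28)^2 0.71^2}{(0.2 - 1.0)^2} = 67". It defines sigma as "variance within the groups", although the equation squares it. Delta is "20 % as per the bioequivalence rule", entered as 0.2. Epsilon is "the absolute values of proportion differences among the groups", entered as 1.0.

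The planning assumptions follow: "The estimated post-intervention prevalence of 20%, 10%, 20% and 50% for the reference, ZN, ZN in MMN and MMN without ZN groups respectively". The section then makes a single power claim, "To show equivalence within 20% rule with 80% power and 5% significance, a sample size of 67 per group was obtained", and adds: "allowing 20% attrition, a sample size of 80 per group is obtained".

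Two other sections bear on this. Randomization allocates three villages to each of the four groups. Data analyses concludes bioequivalence of sprinkles to CSB from the percentages of children with low serum zinc, using a ±20 rule, leaving out children with CRP above 10 mg/l and citing a 95% confidence interval.

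**The concern.** A reader who puts the printed numbers into the printed formula gets a tenth of the stated group size. The epsilon of 1.0 also fails on its own terms. As a difference in proportions it would mean that every child is deficient in one group and none in the other, and it lies far outside the 0.2 margin, where the groups are not equivalent at all.

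The group size and its power are the figures on which the primary objective rests. If 67 does not follow from the stated inputs, neither does the 80% power. The three sprinkles groups have different assumed prevalences, so their chances of showing equivalence to CSB differ, and one power statement cannot serve all of them.

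**Working it through.** **Inputs (all from section 3.4.6).** Z_alpha = 1.64; Z_beta = 1.28; sigma = 0.71; delta = 0.2; epsilon = 1.0 as entered. Assumed prevalences: CSB 20%, ZN 10%, ZN in MMN 20%, MMN without ZN 50%.

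**1. The plan's own figure.** n = (Z_alpha + Z_beta)² × sigma² / (delta − epsilon)²

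- (1.64 + 1.28)² = 2.92² = 8.5264
- 0.71² = 0.5041
- (0.2 − 1.0)² = 0.64
- n = 8.5264 × 0.5041 / 0.64 = 6.72

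The stated 67 is not reproduced.

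**2. Epsilon from the stated prevalences.** Differences from CSB are 0 (ZN in MMN), 0.10 (ZN) and 0.30 (MMN without ZN). The largest difference between any two groups is 0.50 − 0.10 = 0.40. Keeping the printed Z values and sigma, the numerator is 8.5264 × 0.5041 = 4.298:

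| epsilon | (0.2 − epsilon)² | n |
|---|---|---|
| 0 | 0.04 | 107.5, so 108 |
| 0.10 | 0.01 | 429.8, so 430 |
| 0.30 (outside the margin) | 0.01 | 430, without meaning for equivalence |
| 0.40 (outside the margin) | 0.04 | 108, without meaning for equivalence |

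Reading 1.0 as a slip for 0.1 therefore gives 430. To obtain 67, |0.2 − epsilon| must be √(4.298/67) = 0.253, so epsilon would be about 0.45, which no pair of groups supports.

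**3. Where a figure near 67 can come from.** Take the variance sum p1q1 + p2q2 from the assumed prevalences.

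- ZN in MMN vs CSB (20% vs 20%): 0.16 + 0.16 = 0.32, epsilon 0. n = 8.5264 × 0.32 / 0.04 = 68.2, so 69.
- ZN vs CSB (10% vs 20%): 0.09 + 0.16 = 0.25, epsilon 0.10. For 80% power with Z_beta = 0.84, n = 2.48² × 0.25 / 0.01 = 153.8, so 154. With Z_beta = 1.28, n = 8.5264 × 0.25 / 0.01 = 213.2, so 214.

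**4. Power that the planned size delivers.** 80 per group less 20% leaves 80 × 0.8 = 64. Assumed reading: two one-sided tests (TOST) at 5% (Z = 1.645), absolute margin 0.20, independent children. Power = Φ((0.2 − ε)/SE − 1.645) + Φ((0.2 + ε)/SE − 1.645) − 1.

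- ZN in MMN: SE = √(0.32/64) = 0.0707; 2 × Φ(1.184) − 1 = 0.76.
- ZN: SE = √(0.25/64) = 0.0625; Φ(−0.045) + Φ(3.155) − 1 = 0.48.

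At 67 per group the same formula gives 79% and 50%.

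**5. Clustering.** The documents give no intracluster correlation (ICC), so 0.01 to 0.05 is an assumed range. With 64/3 = 21.3 children per village, the design effect is 1 + 20.3 × ICC.

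| ICC (assumed) | design effect | effective n | ZN in MMN | ZN |
|---|---|---|---|---|
| 0.01 | 1.20 | 53.2 | 65% | 42% |
| 0.02 | 1.41 | 45.5 | 54% | 38% |
| 0.05 | 2.02 | 31.7 | 27% | 26% |

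These figures include no penalty for having only three clusters per group, and no loss from the CRP exclusion.

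**The case against.** The strongest defence is that 67 is close to a sound equivalence calculation. For ZN in MMN against CSB, with no true difference, Z_beta = 1.28 is the right value for 80% power under TOST, and n comes to 69. On that view only the printed equation is faulty, not the group size.

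Part of this stands. A reader might infer from step 1 that about 7 children per group would do, or that 67 is a tenfold overestimate. The documents do not support that: 6.7 rests on an impossible epsilon and is not a usable sample size. Nor is 1.28 an error in itself; it is a convention that the section should state. But the defence needs a variance (0.32) and an epsilon (0) that the section does not print, and it covers one of the three sprinkles groups.

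A reader might go on to call ZN in MMN vs CSB the comparison powered at 80%. That does not hold either. With 64 children per group it is below 80% even if they are independent, and lower again with three villages per group.

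A second objection is that the power figures depend on how the decision rule is read, since Data analyses names neither TOST nor a 90% interval. This also stands. If the 95% interval mentioned there must lie within ±20 points, power at 67 independent children per group is about 65% (ZN in MMN) and 37% (ZN). If only the observed percentages had to be within 20 points, ZN would pass about 95% of the time. The 1.64 in the equation favours the one-sided 5% reading but does not settle it.

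Finally, 0.71² is close to 2 × 0.5 × 0.5, which suggests a variance taken at 50% prevalence in both groups. The section does not say so, and the conclusion does not need it.

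**Conclusion.** The point holds and should be corrected before the section is relied on. Two findings need no assumption: the printed equation gives 6.7 rather than 67, and epsilon = 1.0 contradicts both its own definition and the assumed prevalences. With the printed Z values and sigma, no difference among those prevalences gives 67 (108 for epsilon 0, 430 for epsilon 0.10). The claim of 80% power at 67 per group is therefore unsupported as written.

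The size of the shortfall depends on assumptions. Under one-sided 5% TOST with an absolute 20-point margin, 64 independent children per group give about 76% for ZN in MMN and 48% for ZN. Over an assumed ICC range of 0.01 to 0.05 these become about 65% to 27% and 42% to 26%. MMN without ZN, at 50% against 20%, is 30 points from CSB and so outside the margin by the protocol's own assumption; an equivalence power claim cannot apply to it.

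**What to change.** Rewrite section 3.4.6:

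- Replace the equation with one calculation per comparison, using the stated prevalences: variance p1q1 + p2q2, with epsilon 0 for ZN in MMN vs CSB and 0.10 for ZN vs CSB.
- State one power convention and one confidence interval, and make both match the decision rule in Data analyses, including whether the 20 is an absolute margin in percentage points.
- Report the power delivered by the planned 80 per group, that is 64 after attrition and fewer after the CRP exclusion, with a design effect for three villages per group and the assumed ICC range shown.
- Say that MMN without ZN lies outside the margin by assumption and is not covered by the equivalence power claim.
- Do not describe any comparison as powered at 80%.

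The cost is one rewritten section. Restating the power adds no children, but the protocol will show less favourable power for both zinc comparisons.

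### The sample size and its 80% power treat children as individually randomised, although only three villages per arm are randomised

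*Protocol*

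**What the plan says.** Under Study design, the trial is a "cluster randomized bioequivalence trial with four study groups". Under Randomization, "Villages rather than study subjects will be randomized", and "Three villages will be randomly allocated to each of the 4 study groups".

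Section 3.4.6 (Sample size determination) counts a different unit: "n = No. of study subjects per group". Its formula uses two normal deviates, a within-group sigma and a margin of 20%. Neither the formula nor its text contains an ICC, a design effect, a cluster size or a number of clusters. The section concludes that "with 80% power and 5% significance, a sample size of 67 per group was obtained" and raises 67 to 80 for 20% attrition, which is the only inflation. The assumed post-intervention prevalences of zinc deficiency are 20% (CSB reference), 10% (zinc), 20% (zinc in multiple micronutrients) and 50% (multiple micronutrients without zinc).

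Under Data analyses, bioequivalence is to be concluded if the percentages of zinc-deficient children are within a ±20 rule, after excluding children with CRP above 10 mg/l.

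**The concern.** Children in one village share food supply, sanitation, infection exposure and a feeding centre, so their outcomes are likely to be correlated. A formula for independent children then understates the variance of each group's percentage. With three villages per arm, the between-village variance is also estimated from very few units, so normal quantiles are too small for a village-level analysis.

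What is at stake is how an equivalence result is read. If the interval for a difference is wide because there are few villages, failing to show equivalence mainly reflects imprecision. A reader told that the trial had 80% power would take the same result as evidence that sprinkles and CSB differ. This cannot be left to a statistical analysis plan, because the protocol itself fixes both the number and the power claim.

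**Working it through.** **1. The protocol's own figure.** Inputs from section 3.4.6: deviates 1.64 and 1.28, sigma 0.71, denominator (0.2 − 1.0)² = 0.64.

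- As printed: (1.64 + 1.28)² × 0.71² / 0.64 = 8.5264 × 0.5041 / 0.64 = 6.7, not 67.
- With the stated rates 20% vs 20%, zero difference and margin 0.20: 8.5264 × (0.16 + 0.16) / 0.20² = 68.2, close to 67.

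So 67 is, at best, the size for individually randomised children with no true difference. The deviate 1.28 is consistent with 80% power for two one-sided tests at zero difference.

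**2. Design effect.** With m = 67/3 = 22.3 children per village, the design effect is DE = 1 + (m − 1) × ICC. The ICC values are assumed.

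| ICC | DE | Effective n per arm (67/DE) |
|---|---|---|
| 0 | 1.00 | 67 |
| 0.01 | 1.21 | 55 |
| 0.02 | 1.43 | 47 |
| 0.05 | 2.07 | 32 |

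**3. Power with the design effect alone (normal quantiles, 67 per arm).** SE = √[(p₁q₁ + p₂q₂) × DE / n]. The rule is a 90% interval inside ±0.20.

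- 20% vs 20%, ICC 0: SE = √(0.32/67) = 0.0691; power = 2Φ(0.20/0.0691 − 1.645) − 1 = 79%.
- 20% vs 20%, ICC 0.01, 0.02, 0.05: 67%, 56%, 29%.
- 10% vs 20%, ICC 0: SE = √(0.25/67) = 0.0611. Only 0.10 of the margin remains, so power ≈ Φ(0.10/0.0611 − 1.645) = 50%.
- 10% vs 20%, ICC 0.01, 0.02, 0.05: 43%, 39%, 27%.

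**4. Power with a village-level analysis.** Beta-binomial simulation with three equal villages per arm and a 90% t-interval on village percentages inside ±0.20. The variance is either pooled over all 12 villages (12 − 4 = 8 df) or taken from the pair compared (6 − 2 = 4 df). Separate runs agree within about one point.

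| Comparison and method | ICC 0 | 0.01 | 0.02 | 0.05 |
|---|---|---|---|---|
| 20% vs 20%, 8 df, 22 per village | 66% | 53% | 43% | 23% |
| 20% vs 20%, 8 df, 27 per village | 78% | 64% | 52% | 28% |
| 20% vs 20%, 4 df, 22 per village | 55% | 45% | 37% | 22% |
| 10% vs 20%, 4 df, 22 per village | 39% | 34% | 30% | 22% |
| 10% vs 20%, 8 df, 22 per village | 35% | 30% | 25% | 15% |
| Mean 90% half-width, 8 df, 22 per village | 0.13 | 0.14 | 0.15 | 0.18 |

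Twenty-two per village corresponds to 67 per arm, and 27 to all 80 retained.

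**5. Separating the causes for zinc alone vs CSB.** Moving from no true difference to the assumed 10 points takes power from 79% to 50% with no clustering at all. A three-village analysis on 4 df takes it to 39% at ICC 0. Positive ICC then takes it to 34%, 30% and 22%.

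**6. Why the pooled test does worse for that pair.** Mean p(1 − p) is (0.09 + 0.16)/2 = 0.125 for the pair, but (0.16 + 0.09 + 0.16 + 0.25)/4 = 0.165 over four arms, because the arm assumed at 50% enters.

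**The case against.** **The ICC is assumed.** True, and so are equal villages; the protocol gives neither. The size of the loss depends on both. Its existence in a village-level analysis does not: for 20% vs 20% on 8 df, power is 66–78% even at ICC 0.

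**The 80 enrolled children give a cushion.** In part. With all 80 retained, normal quantiles and ICC 0, power for 20% vs 20% is 87%; at ICC 0.01 it is 76% and at 0.05 it is 35%. But the 80 is the attrition allowance: losing the planned 20% leaves 64, and the CRP exclusion removes more.

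**The protocol names no such test.** This stands. Data analyses gives neither two one-sided tests nor a 90% interval, so the power figures describe an assumed village-level interval rule and must be labelled so. If the ±20 rule were applied to observed percentages alone, imprecision could also produce false equivalence; the text does not settle which is meant.

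**A reader might infer that clustering is why zinc alone vs CSB is underpowered.** The protocol's own rates do not support that: 67 independent children already give only about 50%. Nor should 8 df be prescribed throughout, since pooling costs that pair power.

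**A reader might infer that the analysis will ignore villages.** Data analyses does not mention them, but a statistical analysis plan not shown here may.

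**Rewording leaves the trial as imprecise as before.** True. At about 22 children per village, restoring 67 effective children would take 3 × DE = 3.6, 4.3 or 6.2, that is 4, 5 or 7 villages per arm, and all twelve in the sampling frame are already allocated. Adding children has a ceiling: with three villages, effective n cannot exceed 3/ICC, which is 60 at ICC 0.05. Honest wording is therefore the change available within this design.

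**Conclusion.** The point holds. Section 3.4.6 contradicts the Study design and Randomization sections, and its 80% power is not a property of a trial with three villages per arm.

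For 20% vs 20%, power is about 53%, 43% and 23% (22 per village) or 64%, 52% and 28% (27 per village) on 8 df at ICC 0.01, 0.02 and 0.05. With the design effect alone, at 67 per arm, it is 67%, 56% and 29%. For 10% vs 20% it is about 34%, 30% and 22% (4 df) or 30%, 25% and 15% (8 df), from a starting point of only about 50% that has nothing to do with clustering.

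These figures assume the stated prevalences, a margin of 20 absolute percentage points, equal villages, the ICC range and a village-level 90% interval rule. They do not show that the products differ, or that an equivalence claim must fail.

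**What to change.** In section 3.4.6:

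1. State the inputs that 67 rests on. The printed equation gives 6.7; 20% vs 20%, zero difference and margin 0.20 give about 68.
2. Delete the unqualified claim of 80% power.
3. Give the design effect 1 + (m − 1) × ICC over a stated, assumed ICC range.
4. For each comparison, give the power and the expected 90% interval half-width available with three villages per arm (about 0.13–0.18 on 8 df with 22 per village). Use t quantiles whose degrees of freedom match the variance estimate: 4 for one pair, 8 if pooled over twelve villages.
5. For zinc alone vs CSB, show separately the loss due to the assumed 10-point difference and the loss due to clustering and few villages.
6. Label the figures as assuming a village-level confidence-interval rule, and say that an inconclusive result is imprecision, not non-equivalence.

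Cost: protocol wording and a short calculation. No extra children are needed. The stated power becomes visibly less favourable, and the precision of the trial itself does not improve.
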